### Duration of the trial

The recruitment phase of the trial is estimated to last a total of three years, from initiation of the first site to completion for the last patient. This commenced in November 2009. For any given participant the duration of their involvement will be a minimum of 12 months to a maximum of 14 months. Participants’ involvement in the trial will end when they have completed and returned the 12-month assessment questionnaires and travel diary.

### End of the trial

The end of the trial is defined as completion and return of the 12-month assessment questionnaires, scheduled to occur within 2 months after the 12-month assessment date of the last participants.

### Removal of participants from therapy or assessments

No specific withdrawal criteria have been defined for this study. If a participant leaves the study prematurely (that is, prior to completion of the protocol), the primary reason for discontinuation will be determined and recorded, if at all possible. Withdrawn participants are not being replaced. Anonymity of participants will be assured.

### The interventions

A novel rehabilitation technique (intervention) group will be compared to a usual care (control) group.

#### Intervention group

Participants receive what is considered clinically to be routine intervention for outdoor mobility limitations. That is, verbal advice and provision of leaflets provided during the baseline assessment visit. In addition, participants in this group receive up to 12 rehabilitation outdoor mobility sessions of about an hour each over four months. Development of this intervention followed the guidelines for complex interventions [13] using qualitative research findings [14] in the pre-clinical stage to develop ‘barriers and need’ theories. The intervention aims to increase outdoor mobility participation by alleviating physical difficulties, develop skills to maximize the individual's potential and to overcome psychological barriers. A description of the intervention has been published [15]. The main component of the intervention is that therapists go repeatedly with patients to try outdoor mobility, including buses, taxis, walking, voluntary drivers and mobility scooters until they feel confident to go alone or with a companion. The number of interventions depends entirely on the participant. If they feel they do not require any further interventions, for whatever reason, then the interventions can stop. If they feel they require additional intervention, for whatever reason, they can continue the intervention, up to a maximum of 12 visits.

#### Control group

Participants receive what is considered clinically to be routine intervention for outdoor mobility limitations. That is, verbal advice and provision of leaflets provided during the baseline assessment visit.

### Sample size and justification

We intend to recruit 506 participants, 253 into each arm.

Our sample size calculations are based on the primary outcome measure, the Social Function domain of the Short Form 36 version 2 (SF-36v2) at six-month follow-up. A recent study suggested a minimally, clinically important difference (MCID) for the social function domain is 12.5 points [16]. Assuming a power of 90% and a two-sided significance level of 5%, we estimate that to detect a difference in mean SF-36v2 scores of 12.5 points assuming a common standard deviation of 28.2 [17], a sample size of 135 patients per arm is required. This calculation assumes an attrition rate of 20% over the six-month period. Clustering by delivery of treatment was allowed for, using an ICC of 0.02 (obtained from a personal communication from [name]) and a centre effect ICC of 0.04 (obtained from Aberdeen University’s database of ICCs (http://www.abdn.ac.uk/hsru/epp/iccs-web.xls)).

Originally, we calculated our total sample size, which was 676 participants, using the same procedure as above but with seven sites. Due to recruitment being slower than anticipated, we extended the recruitment period and increased the number of centres to 15. Revised sample size calculations were based on a number of scenarios. These calculations indicated that a sample size of 440 would have a power of 86% (assuming no attrition) and a power of 82% (assuming an attrition rate of 20%) to detect a difference in means of 12.5 on the Social Function domain of the Short Form 36 version 2 (SF-36v2) at six-month follow-up if there were 7 centres and, if there were 12 or more centres, the corresponding power would be at least 90% if an attrition rate of 20% was assumed. By increasing the number of centres to 15 we were able to use the later calculations.

Our sample size calculations were based on a number of assumptions and although we used the best estimates we could obtain there was some uncertainty about the true values of the ICCs used to adjust for clustering. We, therefore, decided to be cautious and aimed to recruit a sample size of 506 (440 +15%) to ensure we recruited enough participants.

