### Randomisation

Randomisation is based on a computer generated pseudo-random code using random permuted balanced blocks of randomly varying size, created by the Nottingham Clinical Trials Unit (NCTU) in accordance with their standard operating procedure (SOP) and held on a secure server. The randomisation is stratified by age (<65 years and ≥65 years) and site. Sixty-five years of age was chosen because Mobility Allowance, a monetary allowance is only available under this age and is often used to purchase a car. This is not available for people over 65 years of age. All participants are given the control group standard information prior to randomization in order to minimize performance bias and reduce contamination. Participants are randomly allocated (1:1 ratio) to either the intervention or to the control group. Access to the sequence is confined to the NCTU Data Manager (who is independent from the study team). Investigators/sites access the treatment allocation for each participant by means of a remote, secure, internet-based randomisation system developed and maintained by the NCTU. The sequence of treatment allocations is concealed until interventions have all been assigned and recruitment, data collection and all other trial-related assessments are complete. After confirming study eligibility and obtaining informed consent, the investigator enters basic demographic details into the web-based randomization program. Once these details have been entered irrevocably into the program, the group to which the patient is randomly allocated is provided to the investigator.

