### Assessment of efficacy

#### Analysing primary outcomes

The mean Social Function score of the SF-36v2 will be compared between treatment arms using a multiple membership form of mixed effects, multiple regression analysis adjusting for centre (as a fixed effect), age and baseline Social Function score as covariates and therapist as a multiple membership random effect. Regression coefficients and 95% confidence intervals will be presented. The robustness of these findings will be assessed by repeating the analysis and including baseline variables (such as gender) that are associated with the outcome variable as covariates in the model.

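### The sample-size section counts the centre ICC as a variance inflator although centre is a stratifier and a fixed effect, so the 82% and 86% powers, and the gain credited to more centres, do not fit the design

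*Protocol article*

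**What the plan says.** The protocol article, under Sample size and justification, plans to "detect a difference in mean SF-36v2 scores of 12.5 points assuming a common standard deviation of 28.2". It sets the error rates as "Assuming a power of 90% and a two-sided significance level of 5" per cent, and adds "This calculation assumes an attrition rate of 20% over the six-month period". The unclustered requirement is 135 per arm. Two ICCs then enter the adjustment for clustering: 0.02 for delivery of treatment, and "a centre effect ICC of 0.04".

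The original total was 676, with seven sites. Recruitment was slow, so the recruitment period was extended and centres were added. The revised scenarios state that "a sample size of 440 would have a power of 86% (assuming no attrition) and a power of 82" per cent (20% attrition) with 7 centres, and at least 90% with 12 or more centres and 20% attrition. The section concludes: "By increasing the number of centres to 15 we were able to use the later calculations". The target became 506, which is 440 plus 15%.

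Under Randomisation, individuals are allocated 1:1 and "The randomisation is stratified by age (<65 years and ≥65 years) and site". Under Analysing primary outcomes, the model is described as "adjusting for centre (as a fixed effect), age and baseline Social Function score as covariates", with therapist as a multiple membership random effect. No random treatment-by-centre term is described.

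**The concern.** Both arms are present in every centre. Whatever raises or lowers scores across a whole centre affects both arms alike and drops out of the within-centre treatment difference, which is what a model with fixed centre effects estimates. A centre main-effect ICC therefore cannot inflate the variance of that difference. Yet the section lists the centre ICC among those used to adjust for clustering, and makes power at a fixed 440 depend strongly on the number of centres. That dependence is typical of a design in which centres, not individuals, are randomised.

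At stake is whether the stated power belongs to this trial, and whether the power argument for accepting 440 in place of 676 stands. A reader who wants to know what difference the trial can detect is also given the wrong precision.

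**Working it through.** **Inputs.** Difference 12.5, SD 28.2, two-sided 5%, attrition 20%, therapist ICC 0.02 and centre ICC 0.04, all from Sample size and justification. Therapists per centre (t) are not stated; I assume 1 to 4, each working at one centre. Normal approximation throughout. n is the number analysed per arm and m = n / number of centres.

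**Unclustered size.** 2 × (1.960 + 1.282)² × 28.2² / 12.5² = 107, or 108 with the t correction. 108 / 0.8 = 135 per arm, as stated.

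**Reproducing the stated powers.** Use the centre ICC as an inflator in both arms and the therapist ICC in the intervention arm:

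- DE(control) = 1 + (m − 1) × 0.04
- DE(intervention) = DE(control) + (m/t − 1) × 0.02
- SE = 28.2 × √[(DE(control) + DE(intervention)) / n]
- power = Φ(12.5/SE − 1.96)

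Example: 440, 7 centres, no attrition, t = 2. n = 220 and m = 31.43. DE(control) = 2.217 and DE(intervention) = 2.511. SE = 28.2 × √(4.729/220) = 4.13. Power = 85.6%.

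| 440 participants | Stated | Rebuilt, t = 2 to 3 | Centre ICC alone |
|---|---|---|---|
| 7 centres, no attrition | 86% | 85.6-86.4% | 87.7% |
| 7 centres, 20% attrition | 82% | 82.2-82.9% | 84.3% |
| 12 centres, 20% attrition | at least 90% | 90.6-91.0% | 91.7% |

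The superseded 676 also fits a centre inflator. Solving n = 108 × [1 + (n/7 − 1) × 0.04] gives n = 103.68 / 0.3829 = 270.8 per arm, and 2 × 270.8 / 0.8 = 677.

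**Can the stated powers be reached without the centre ICC?** No. A deliberately conservative variant, with 0.02 in both arms and one cluster per arm per centre, still gives 95.6%, 92.7% and 95.8% for the three rows.

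**Power under the stated design and model.** Drop the centre inflator and keep the therapist ICC in the intervention arm:

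- DE(intervention) = 1 + (m/t − 1) × 0.02
- SE = 28.2 × √[f × (1 + DE(intervention)) / n]

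Here f = 1, or f = 0.96 (that is, 1 − 0.04) if the SD of 28.2 includes between-centre variance that the fixed effects remove. The article does not settle which, so both are shown.

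Example: 440, 7 centres, 20% attrition, t = 2, f = 1. n = 176 and m = 25.14. DE(intervention) = 1.231. SE = 28.2 × √(2.231/176) = 3.18. Power = 97.6%.

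| Scenario | Stated | Range over t = 1 to 4 and both f |
|---|---|---|
| 440, 7 centres, no attrition | 86% | 98.3-99.6% |
| 440, 7 centres, 20% attrition | 82% | 96.2-98.5% |
| 440, 12 centres, 20% attrition | at least 90% | 97.4-98.7% |
| 440, 15 centres, 20% attrition | – | 97.7-98.8% |
| 506, 15 centres, 20% attrition | – | 98.8-99.4% |

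**Gain from 7 to 12 centres (20% attrition).** With f = 1 it is 97.4 − 96.2 = 1.2 points at t = 1, and 98.4 − 98.2 = 0.2 points at t = 4. The article implies at least 90 − 82 = 8 points.

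**Precision at 506, 15 centres, 20% attrition.** The SE is 2.78 to 2.97, against about 3.5 under the rebuilt planning formula. The difference detectable with 90% power is 3.242 × SE = 9.0 to 9.6 points.

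**The case against.** Several stronger readings are tempting, and the article does not support them.

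- **All the power figures are wrong.** A reader might infer this, but at least 90% with 12 or more centres is a lower bound, and 97-99% satisfies it. That is the scenario the trial relies on; 82% and 86% belong to a 7-centre scenario that was dropped.
- **Centres were added because of a false power gain.** The article gives slow recruitment as the reason. The power scenarios supported the smaller total, not the decision to open more centres.
- **The extra precision creates a risk of significance below the 12.5-point MCID.** Any trial with exactly 90% power for its MCID reaches significance at 1.96/3.24 × 12.5 = 7.6 points. For 506 the threshold is about 6.9 points with the rebuilt planning SE (1.96 × 3.5) and 5.4 to 5.8 with the corrected one (1.96 × 2.78 to 2.97). The error shifts the threshold by a little over a point; it does not create the issue. The plan also reports coefficients with confidence intervals.
- **The exact planning formula is known.** It is not. With one therapist per centre the rebuilt formula gives 83.3%, 79.9% and 89.3%, missing all three stated figures. The 676 fits best with the centre ICC alone: 90.3%, against 88.2% once the therapist term for t = 2 is added. What stands is narrower: some inflation by the centre ICC is needed to reach the stated powers.

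The best defence is that 0.04 was meant as between-centre variation in the treatment effect, which could justify inflation. But the article calls it a centre effect, and the model has no such term. The therapist random effect would absorb part of that variation, and with one therapist per centre the two could not be separated. The section and the model would still need reconciling.

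The article admits uncertainty about the ICC values and adds 15% for it. That is prudent, but it concerns the size of the ICCs, not whether the centre ICC belongs in the design effect.

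**Conclusion.** The point holds as a mismatch between the power calculation and the design, not as an arithmetic slip. The 82% and 86% understate power by roughly 14 to 16 and 12 to 14 points respectively, and the gain credited to more centres is about 1 point or less, not at least 8. This rests on the inference that the centre ICC was used as an inflator, on 1 to 4 therapists per centre, and on the article's own difference, SD, ICCs and attrition.

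The error is conservative. A reader might conclude that the sample size or the primary analysis is invalid; neither is. On these inputs 506 is not too few, and the planned model estimates the treatment effect validly as it stands. The severity is low: what needs correcting is the statement of power and of what the trial can detect.

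**What to change.** Leave the account of how 440 and 506 were set, since it records what was done. Add a short correction to the protocol and the final report that:

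- drops the centre ICC from the design effect, because allocation is stratified by site and centre is a fixed effect;
- keeps the therapist ICC of 0.02 in the intervention arm and states the assumed number of therapists per centre;
- restates power, at 15 centres with 20% attrition, as about 98% for 440 and about 99% for 506, with a 90%-power detectable difference for 506 of about 9.0 to 9.6 points.

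If 0.04 was meant as variation in the treatment effect between centres, say so and reconcile it with the primary model, noting that such a term overlaps with the therapist random effect where centres have one or few therapists.

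The cost is one paragraph. Recruitment does not change, and the primary analysis changes only if that alternative meaning of 0.04 is adopted.

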### Statistical analysis

Data are stored in a Microsoft Access Database and analyzed using the statistical package STATA (StataCorp, Texas, USA). Paper records are kept in a locked cabinet, separate from any identifiable information, such as the consent forms. A full data analysis plan has been produced and agreed with the Trial Steering Group. Outcome measures are recorded at 6 and 12 months but the primary time point of interest is 6 months. However, this data will not be analysed until all study data have been collected. The study report will be produced according to the CONSORT recommendations [18].

#### Descriptive analyses

Continuous data that are approximately, normally distributed will be summarised in terms of the mean, standard deviation and the number of observations. Skewed data will be presented in terms of the median, lower and upper quartiles, minimum, maximum and number of observations. Categorical data will be summarised in terms of frequency counts and percentages.

#### Comparisons between treatment arms

Analyses will be undertaken on an intention to treat basis in that participants will be analysed in the group to which they were randomised regardless of whether they received the intervention or not. Two-sided tests will be used to test statistical significance at the 5% level.

### Assessment of efficacy

#### Analysing primary outcomes

The mean Social Function score of the SF-36v2 will be compared between treatment arms using a multiple membership form of mixed effects, multiple regression analysis adjusting for centre (as a fixed effect), age and baseline Social Function score as covariates and therapist as a multiple membership random effect. Regression coefficients and 95% confidence intervals will be presented. The robustness of these findings will be assessed by repeating the analysis and including baseline variables (such as gender) that are associated with the outcome variable as covariates in the model.

#### Analysing secondary outcomes

The outcome variables mobility measured with the Rivermead Mobility Index [8] number of outdoor journeys taken, functional ability measured by the Nottingham Extended Activities of Daily Living Scale [19]; mood and carer psychological distress measured by the General Health Questionnaire 12 [9] will be analysed using the same method as for the primary outcome measure. In all analyses, an adjustment for centre, therapist effect, age and baseline value will be made.

The proportion of participants saying they get out of the house as often as they would like will be compared between treatment arms using a mixed effects logistic regression analysis adjusting for centre (as a fixed effect), age and whether or not they get out of the house as often as they would like as recorded at baseline. Odds ratios and 95% confidence intervals will be presented.

The robustness of the findings for all secondary outcomes will be assessed by repeating the analysis and including baseline variables, (such as gender), that are associated with the outcome variable as covariates in the model.

We acknowledge the potential for type 1 errors associated with significance testing for multiple end points. We will, therefore, consider our analyses of the secondary outcome measures to be partly exploratory in nature, and partly confirmatory of our findings for the primary outcome measure.

### Health economic evaluation

An economic evaluation will be a major element of the project. This component of the study aims to extend the evidence base by estimating for the first time the incremental cost-effectiveness of an outdoor mobility rehabilitation intervention, compared to usual care, from a health and personal social services perspective for the trial period. In addition, the patient and carer perspective will be examined separately.

The EQ-5D includes five pertinent dimensions, (ability to perform usual activities, mobility, anxiety and depression, pain and self-care), each with three levels of severity (no problems, some/moderate problems and severe/extreme problems). Responses to these five dimensions will be converted into one of 243 different EQ-5D health state descriptions, which range between no problems on all five dimensions (11111) and severe/extreme problems on all five dimensions (33333). We will use the York A1 tariff to assign a utility score to each of these states. The SF-6D is measured using the responses to 11 of the questions on the SF-36 questionnaire for use in cost utility analyses [20]. The SF-6D is composed of six dimensions (physical functioning, role limitations, social functioning, pain, mental health and vitality), which have between four and six severity levels. It, thereby, has 18,000 potential health states and scores for these states have been estimated [6]. Both measures are being used at baseline, 6 and 12 months. Quality Adjusted Life Year (QALYs) will be estimated over the trial period between the comparator interventions in order to provide a cost per QALY for the getting out of your house intervention. As a generic measure of outcome this analysis will enable the results to be compared to that of other economic evaluations for stroke and other conditions, in order to assess whether allocation of resources to a getting out of the house intervention offers value for money compared to other potential uses of the resources.

As the EQ-5D and SF-6D utility measures are based on both different health state descriptions, and use different valuation techniques, they can produce different utility scores for the same group of patients. This study will seek to investigate which of these two outcome measures is appropriate using certain published criteria and to explore the impact choice of utility measure has on estimates of cost-utility since further research has been argued as justified in these areas.

Although not anticipated, censored data will be adjusted using appropriate published techniques [21] should this be necessary. If non-dominance occurs (that is, if costs are greater and the intervention is more effective or if the intervention is cheaper and less effective) an incremental cost-effectiveness ratio (the ratio of change in cost divided by change in benefit) will be produced. The confidence region around the incremental cost effectiveness ratio will be estimated using appropriate statistical techniques, such as the non-parametric bootstrap method. This stochastic analysis will enable a cost effectiveness acceptability curve to be produced illustrating the uncertainty surrounding the optimal decision. Probabilistic sensitivity analysis will be undertaken to test the robustness of the results. Estimates of the incremental cost, incremental costs effectiveness and the uncertainty around these estimates will enable us to examine whether "The getting out of the house intervention" offers value for money.

### Fidelity of treatment

The rehabilitation staff providing the treatment are completing an intervention record for each participant and recording number and duration of treatment. These records are monitored against a predefined checklist to make sure the intervention is being delivered according to the protocol. In addition, a selection of therapy visits are observed and scored against a predefined checklist.

### Assessment of safety and adverse events

The main risk associated with this intervention is an increased risk of falling, as participants are being encouraged to become more mobile. So, as all falls will be self-reported on the travel diary, the only adverse events we will record will be any falls within the intervention group that required the assistance of a healthcare professional. To capture these events the therapist will ask, subsequent to the first visit, “Have you had any falls since my last visit?” The occurrence of a serious adverse event as a result of participation within this study is not expected so no serious adverse event data will be collected.

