#### Travel diaries

A travel diary is being completed by all participants on a monthly basis. This is in the form of a calendar with the participants entering the number of journeys made on the calendar for that particular day. In addition, in order for the study team to assess safety, participants indicate when they have had a fall on a particular day. The participant is provided with 12 calendar months’ worth of travel diary. Training is provided at baseline assessment in the completion and return of the travel diaries. At the end of each month participants are asked to return that month of the calendar to the research team. A reminder letter is sent to the participant, along with a reply paid envelope, a short time before the previous month’s diary is due for return.

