### Trial management

The trial will be managed by the Trial Management Group. The Trial Steering Committee and Data Monitoring Committee will be combined as a risk assessment has been completed and as the risk to participants is low we consider that the two committees will work best if they are merged. This will be called the Trial Steering and Data Committee (TSDC). The TSDC will meet independently prior to the start of the study and will agree to terms of reference and will monitor unblinded data and the conduct of the study. Only the TSDC will have access to unblinded data until the final outcome assessment has been completed. The TSDC will recommend discontinuation of the study if significant ethical or safety concerns arise or if there is very clear evidence of benefit (clinical or statistical) prior to completion of the study. The sponsor is the University of Nottingham, which will clarify with the funding body (the HTA) and local centre research and development departments their precise responsibilities. The CI, delegated by the Sponsor, is responsible for the proper conduct and management of the trial.

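### Adverse event recording is confined to falls and no serious adverse events are collected, so a non-fatal, non-fall injury during outdoor travel does not reach the safety data

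*Protocol article*

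**What the plan says.** The section on assessment of safety and adverse events starts from a stated hazard: "The main risk associated with this intervention is an increased risk of falling". It then sets a closed rule: "the only adverse events we will record will be any falls within the intervention group that required the assistance of a healthcare professional". The means of finding these events is one question put by the therapist at visits after the first: "Have you had any falls since my last visit". On serious adverse events, it says that their occurrence through participation "is not expected so no serious adverse event data will be collected".

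The description of the intervention group says that therapists repeatedly take participants out, "including buses, taxis, walking, voluntary drivers and mobility scooters until they feel confident to go alone or with a companion".

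The travel diary, kept in both arms, counts journeys, and in it "participants indicate when they have had a fall on a particular day". Under trial management, the TSDC sees unblinded data and has a safety remit: "The TSDC will recommend discontinuation of the study if significant ethical or safety concerns arise".

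**The concern.** Naming falls as the main risk accepts that there may be others, but the recording rule leaves room for none. Travel by vehicle and scooter carries its own foreseeable hazards: collisions, injury as a passenger, injury while handling a scooter. The intervention deliberately increases exposure to them, first accompanied and later, for some participants, alone.

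Two things are at stake. The committee is asked to act on safety concerns but is given no organised information on one kind of harm that the treatment could plausibly cause. And a final report with no non-fall injuries would reflect the definition, not observation. The problem is the type of event recorded, so recording falls equally in both arms would not cure it.

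**Working it through.** The plan states no figure on this point, so the check is to trace one type of event through every data source the article describes. Take a participant in the intervention group who is injured in a taxi or scooter collision without falling, is admitted to hospital, and survives.

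- **Adverse event** (safety section): not recorded, because it is not a fall.
- **Serious adverse event** (same section): not recorded, because none are collected. For an admission this sentence matters most; widening the adverse event definition alone would leave it in force.
- **Therapist's question** (same section): asks about falls only. It also ends with the visits, which run for up to four months of a 12-month follow-up, so later unaccompanied travel is out of its reach.
- **Travel diary**: journeys and falls only.
- **Intervention record** (fidelity section): described as number and duration of treatment, checked for adherence to the protocol.
- **Questionnaires at 6 and 12 months** (health economics section): the admission may be counted in the amount of care used. The article does not say that the cause is recorded, and the stated purpose is costing.
- **National register deaths** (outcome section): does not apply to a survivor. For a fatal injury the death would appear, but recording of its cause is not stated.
- **Reason for discontinuation** (section on removal of participants): applies only if the person leaves the study, and only where the reason can be established.

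No source described carries this event as safety data with its cause. The same narrow definition governs the section that allows withdrawal after an adverse event.

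**Illustrative size.** Inputs from the sample size section: 253 participants per arm, 20% attrition. From the intervention section: at most 12 sessions.

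- Maximum number of sessions: 253 × 12 = 3,036. This is a ceiling, since participants may stop earlier.
- If injuries were recorded and none occurred, the approximate 95% upper bound by the rule of three is 3/n. With n = 253: 3/253 = 1.19%. The exact form, 1 − 0.05^(1/253), gives 1.18%.
- With 20% attrition: n = 253 × 0.8 ≈ 202, and 3/202 = 1.49%.

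These are single-arm bounds. They show what recording could support; they do not estimate the risk.

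**The case against.** The other side has four serious arguments.

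1. **Other channels exist.** A reader might infer from the safety section that travel injuries are never recorded and that the committee cannot act on them. The article does not support that. Tipping off a scooter, falling while boarding a bus or being knocked down can be entered as a fall. Deaths are obtained from the register, an admission may show in care use, and an injury that causes withdrawal may appear as the reason. A therapist is present at practice sessions and some visits are observed. The TSDC has a general remit, and the sponsor may stop the trial for safety. All of this stands. What it leaves is indirect: none of these sources is stated to be reviewed as safety data, and for deaths and care use no recording of cause is stated.

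2. **The restriction was reasoned.** Falling is named as the main risk, and a risk assessment rated the risk to participants as low. Targeted recording can be right in a low-risk trial, and the documents give no rate for non-fall injury. But a low rating is an expectation, and it is a weak reason to leave out a foreseeable hazard of what the treatment asks people to do.

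3. **The figures prove no harm.** Correct. Neither 3,036 sessions nor the 1.2% bound is evidence that any injury occurred, and the point does not depend on them.

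4. **It is late.** Participants were identified up to July 2011, sessions fall within four months of recruitment, and the trial status section reports follow-up continuing to the end of August 2012. On those dates a new line on the therapist's record may capture little or nothing, and most 6-month forms may already be out. This stands, and it limits what an amendment can recover.

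The fact that an article condenses a fuller protocol does not answer the point: the restriction is stated outright and is not inferred from silence.

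**Conclusion.** The concern holds in a limited form. A non-fatal, non-fall injury during outdoor travel is recorded as neither an adverse nor a serious adverse event, so the TSDC has no systematic, cause-specific data on a foreseeable hazard of the intervention. Total absence of information, or a committee unable to act, would be too strong a conclusion.

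The primary analysis, sample size and power are untouched; the weakness is in safety monitoring and in what the report can say about harm. The conclusion rests on reading the safety section's restriction as exhaustive, which its wording requires, and on care use and deaths not being collected by cause, which the article leaves unstated. If the full protocol does collect causes and sends them to the committee, the gap narrows. The upper bounds of about 1.2% and 1.5% are illustrative and assume complete ascertainment among 253 and about 202 treated participants respectively.

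**What to change.** In the safety section:

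- Define the recorded event as any fall, or any other injury while out of the house or travelling, that needed treatment.
- Delete the statement that serious adverse event data will not be collected, at least for such injuries leading to admission or death.
- Collect the event in both arms with one added item in the 6- and 12-month questionnaires that everyone already receives.
- Add a line to the therapist's intervention record for any injury during a session.
- Tabulate the results by arm for the TSDC.

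The cost is a protocol amendment, one questionnaire item and one line on an existing form. The downsides are a slightly longer questionnaire and recall over about six months by participants who know their allocation, so a comparison between arms would be open to reporting bias. The therapist's line exists in the intervention arm only and should be shown separately from the questionnaire counts.

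With recruitment and treatment largely or wholly past, the new item may reach only the forms still to be sent. For participants not covered, the report should state that non-fall injury was not ascertained, and should not present the absence of records as absence of harm.
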